### Data collection and management

Follow-up data will be collected by trained clinical research technicians on an electronical case-report-form (eCRF). To avoid women lost to follow-up, they will track women deliveries, especially when taking place outside the investigation centres. eCRFs shall be periodically cross-checked for completeness. A data management plan will be written and follow during all the data management and analysis process.

### Confidentiality and data handling

Data will be handled according to the French law. The eCRFs will be hosted by a service provider into a secured electronic system via a web navigator and protected by an individual password for each investigator and clinical research technician. Participant’s identifying information will be replaced by an unrelated sequence of characters to ensure confidentiality. The steering committee will have access to the full trial dataset. The trial database file will be stored for 15 years. The sponsor is the owner of the data.

### Statistical analysis

#### Sample size

To study the non-inferiority of the 50% reduced betamethasone dose regimen, we will test the alternative hypothesis that the difference in failure rate between the half-dose and the full-dose arm do not exceed 4% (corresponding to a Relative Risk of 1.20). This non-inferiority margin has been obtained through a consensus between the investigators of the GROG, neonatologists and the methodologists of the study, considering that a 4% difference is the smallest value that would be clinically relevant between arms and correspond to the preservation of a 70% of the effects of the full dose betamethasone regimen over placebo. Indeed, in the French Epipage2 study (2011) [51], 62% of the neonates exposed to antenatal betamethasone and born before 32 weeks of gestation from a singleton pregnancy received exogenous surfactant. Assuming that 33% (conservative hypothesis) of the randomised women will indeed deliver before 32 weeks, we estimated that 20% of the included pregnant women receiving the full betamethasone dose regimen would have a neonate with severe RDS, defined as the need for exogenous intra-tracheal surfactant. According to the literature, ACS is responsible for an average relative risk of RDS of 0.66 (95% CI 0.56 to 0.77), compared to placebo [8, 52]. Assuming a prevalence of severe RDS of 20% in the full dose betamethasone regimen, to preserve 67% of the upper bound for the historical difference between full dose and placebo (i.e. 0.67 x (0.20–0.20/0.77)) gave a margin of 4% (or expressed as Relative Risk (20 + 4) / 20 = 1.20). Thus, 1571 patients in each treatment group are required to test the non-inferiority hypothesis, with a 1-sided type-1 error of 0.025, a power of 0.80, and a non-inferiority margin equal to 4% [53].

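### The margin derivation labels the share of the steroid effect that may be lost as the share preserved: at the bound it names, 4 points preserves about 33%, not 67% or 70%

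*Protocol article*

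**What the plan says.** All the relevant statements stand in the protocol article, Statistical analysis, Sample size.

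- **Two reasons are given for the margin.** One is a consensus among investigators, neonatologists and methodologists about clinical relevance. The other is effect preservation: 4 points is said to "correspond to the preservation of a 70% of the effects of the full dose betamethasone regimen over placebo".
- **Historical effect:** "ACS is responsible for an average relative risk of RDS of 0.66 (95% CI 0.56 to 0.77), compared to placebo".
- **Control rate:** "Assuming a prevalence of severe RDS of 20% in the full dose betamethasone regimen".
- **Derivation:** the aim is "to preserve 67% of the upper bound for the historical difference between full dose and placebo", followed by the formula and its result in percent, "i.e. 0.67 x (0.20–0.20/0.77)) gave a margin of 4".
- **Sample size:** 1571 per arm, "with a 1-sided type-1 error of 0.025", "a power of 0.80" and the 4-point margin.

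The same margin appears in the Abstract and in Aims of the trial, without the preservation argument.

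**The concern.** A non-inferiority margin is the largest loss that the trial will tolerate. To preserve a fraction f of a historical effect M1, the margin has to be (1 − f) × M1. The protocol multiplies M1 by 0.67 and calls the result preserving 67%. Multiplying by 0.67 gives the part that may be given up, and the part kept is the remaining 0.33.

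The margin defines the primary claim and one of the two stated grounds for stopping early. A reader who takes the Sample size section at its word would believe that a positive result secures about two thirds of the conservatively estimated steroid benefit. On the protocol's own figures, it would only exclude losing more than about two thirds of that benefit.

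**Working it through.** **Inputs (all from Sample size unless noted).** Full-dose severe RDS rate 0.20. Historical relative risk 0.66, 95% CI 0.56 to 0.77. Margin 0.04. One-sided alpha 0.025, power 0.80. From Background, Benefits of antenatal corticosteroids: a 38% reduction in RDS in singleton pregnancies, which implies a relative risk of 1 − 0.38 = 0.62.

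**1. Reproduce the plan's margin.** Placebo rate at the conservative bound: 0.20/0.77 = 0.2597. Effect M1 = 0.2597 − 0.20 = 0.0597. Then 0.67 × 0.0597 = 0.0400. The printed formula subtracts in the other order and so gives −0.0400; the size is the stated 4 points.

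**2. Reproduce the plan's sample size.** With equal true rates of 0.20 and the unpooled normal approximation:

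n = 2 × 0.20 × 0.80 × (1.960 + 0.842)² / 0.04² = 0.32 × 7.849 / 0.0016 ≈ 1570 per arm, against 1571 stated.

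**3. Fraction preserved by a 4-point margin.** Difference scale: 1 − 0.04/(0.20/RR − 0.20). Log relative-risk scale: 1 − ln(1.20)/ln(1/RR).

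| Historical RR | Source | Effect (points) | Lost | Preserved | Preserved, log scale |
|---|---|---|---|---|---|
| 0.77 | conservative bound, used in the derivation | 5.97 | 67% | 33% | 30% |
| 0.66 | point estimate | 10.30 | 39% | 61% | 56% |
| 0.62 | implied by the 38% singleton reduction | 12.26 | 33% | 67% | 62% |
| 0.56 | optimistic bound | 15.71 | 25% | 75% | 69% |

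In event rates at the named bound: full dose 20%, placebo about 26%, tolerated half-dose rate up to 24%. Of about 6 points of benefit, about 2 are kept.

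**4. Size of the gap between label and formula.** Preserving 67% at RR 0.77 would mean a margin of 0.33 × 5.97 = 1.97 points (relative risk about 1.10). By the formula in step 2 that needs about 6,460 per arm, and 1571 per arm would have about 28% power against it. The discrepancy is therefore not rounding.

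**The case against.** Several points on the other side have weight.

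- **The margin has a second rationale.** The section also rests 4 points on clinical consensus. A reader might infer that the whole basis for the primary claim falls. It does not: the arithmetic touches only the effect-preservation argument.
- **One figure in the document does give 67%.** The singleton reduction of 38% implies RR 0.62, at which 4 points preserves about 67% on the difference scale. This stands as a number and belongs in the restated text. It does not rescue the derivation, because 0.62 is a point estimate and the sentence names the conservative bound and uses 0.77.
- **The 70% has no stated origin.** On the log scale at RR 0.77 the share lost is ln(1.20)/ln(1/0.77) = 0.70, so a reader might infer the same inversion on another scale. It could as well be a loose rounding of 67%. The document gives no formula, bound or scale for it. What can be shown is that 70% is not preserved at RR 0.77 or 0.66, and that it differs from the 67% in the same section.
- **No preserved-fraction conclusion is planned.** Final analyses tests against the 4-point margin, and the Discussion speaks only of non-inferiority. The planned conclusion therefore needs no rewording.
- **The trial is not shown to be too small.** The figure of about 6,460 per arm might suggest so. It applies only if a 67% preservation target is binding. For the 4-point margin that the trial tests, 1571 is right.

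**Conclusion.** The point holds in a narrow form. The derivation sentence calls the conceded fraction the preserved fraction. At the bound the protocol names, 4 points concedes about 67% of the historical effect and preserves about 33%; at its point estimate it preserves about 61%. The separate 70% is unsupported at either value.

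The sample size for a 4-point margin, the type I error against that margin and the consensus rationale are unaffected.

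The percentages rest on two assumptions: a full-dose rate of 20%, and that a historical relative risk for RDS carries over to this trial's endpoint, surfactant within 48 hours. Both are the protocol's own working assumptions, but they make the preserved fractions conditional figures rather than established ones.

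**What to change.** Keep the 4-point margin and the sample size. In Sample size:

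1. Delete both preservation statements (the 67% and the 70%).
2. State instead that, assuming a 20% full-dose rate and that the historical relative risk for RDS applies to surfactant use, a 4-point margin preserves about 33% of the effect at the conservative bound (RR 0.77) and about 61% at the point estimate (RR 0.66), or about 67% if the singleton RR of 0.62 is used.
3. State that the margin rests on clinical consensus, and that 4 points is still considered acceptable on that footing. Rewording without this re-justification would leave the margin's rationale incomplete.

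Any report or approval document that cites effect preservation should carry the same figures.

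**Cost.** No extra patients and no change to the test. The stated figure is less favourable. Under Ethics, changes to the statistical plan need approval by the steering committee, the sponsor, the French medicines agency and the DSMB, so re-approval is needed if that plan, which is not available here, contains the same text.

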#### Analysis population

The primary non-inferiority statistical analysis will be performed according to both the intention-to-treat and per protocol principle, as it is recommended for non-inferiority trials [54]. The intention-to-treat population will included all randomised patients according to the treatment group where they have been randomly assigned, regardless of what treatment, if any, they received. The per protocol (PP) analysis will included only the participants who fulfill the protocol in terms of eligibility, interventions and outcome assessment: the women will be excluded from this analysis if they did not fulfill the eligibility criteria, if they did not receive any intervention after randomisation, if they received the intervention of the opposite arm as first and/or rescue course, and if the intervention was overdosed or intravenous. Women who received the first course as they were randomised but who received an incomplete rescue course will be analyzed in their randomisation arm.

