### Study interventions

Women of the standard full dose group will receive a second intramuscular injection of 11.4 mg of betamethasone (Celestene Chronodose, MSD France) 24 h after the first injection of betamethasone.

Women of the experimental half dose group will receive a second intramuscular injection of serum saline 24 h after the first injection of betamethasone.

Women of both groups justifying a rescue course of ACS are allocated a “rescue course treatment pack” from the same treatment group. All others concomitant care and interventions are permitted during the trial and none are prohibited.

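### The per-protocol rescue criterion is worded alike for both arms, but a full active rescue course given outside the trial packs removes half-dose women and keeps full-dose women

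*Protocol article*

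**What the plan says.** The protocol article, Analysis population, states that the primary non-inferiority analysis "will be performed according to both the intention-to-treat and per protocol principle". Per-protocol exclusions include women who failed eligibility, received no intervention after randomisation, or received an overdosed or intravenous intervention. They also include women to whom this applies: "if they received the intervention of the opposite arm as first and/or rescue course". A further sentence covers partial rescue: "Women who received the first course as they were randomised but who received an incomplete rescue course will be analyzed in their randomisation arm".

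Study interventions defines the regimens. Full-dose women "will receive a second intramuscular injection of 11.4 mg of betamethasone". For the other arm: "Women of the experimental half dose group will receive a second intramuscular injection of serum saline 24 h after the first injection of betamethasone". Planned rescue is masked and arm-specific: "Women of both groups justifying a rescue course of ACS are allocated a" rescue pack from their own treatment group. The next sentence reads: "All others concomitant care and interventions are permitted during the trial and none are prohibited".

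Data collection and management expects some births elsewhere; of the research technicians it says that "they will track women deliveries, especially when taking place outside the investigation centres". The section on allocation and blinding masks patients, care providers and outcome assessors.

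**The concern.** The criterion judges a rescue course by whether it matches the assigned arm. An ordinary full course (two active injections) from outside the trial packs matches the full-dose arm and contradicts the half-dose arm, so one event leads to two outcomes. The mirror case, a full-dose woman who receives one active injection and then saline as rescue, essentially requires a wrong study pack, because ordinary care does not give saline as a second injection.

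Masked clinicians would give off-pack courses at similar rates in both arms. Removing those women from one arm only is selection after randomisation. Rescue goes to women again thought to be at risk of early delivery, so their risk of severe respiratory distress syndrome (RDS) may well differ from the arm average. At stake is one of the two analyses of the primary question, and the one intended to guard against dilution.

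**Working it through.** **Classification by rescue exposure actually received**, applying Analysis population to the regimens in Study interventions:

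| Rescue received | Half-dose woman | Full-dose woman |
|---|---|---|
| Two active injections | dropped | kept |
| One active, then saline (half-dose pack) | kept | dropped |
| Incomplete course | kept | kept |

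If rescue comes only from trial packs, rows 1 and 2 both need a pack error and the rule is balanced. Off-pack courses fall in row 1, so they act on one arm.

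**The plan's own figure.** Inputs from Sample size: 20% failure, margin 4 points, one-sided 0.025, power 0.80. No expected difference is stated, so 0 is assumed.
n = (1.96 + 0.8416)² × 2 × 0.20 × 0.80 / 0.04² = 1569.8, or 1570 per arm. The plan states 1571, at which power is 80.0%. The figure reproduces and does not depend on the present point.

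**Illustration.** Let f be the share of each arm given an off-pack full rescue course and r the risk of severe RDS in those women. Neither is in the documents; both are assumed. The top value of r, 62%, is the surfactant rate that Sample size gives for singleton births before 32 weeks. With both arms at 20% and removal from the half-dose arm only:

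half-dose per-protocol rate = (0.20 − f × r) / (1 − f); the full-dose rate stays at 20%.

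| f | r | Half-dose rate | Shift (points) |
|---|---|---|---|
| 1% | 40% | 0.196/0.99 = 19.80% | −0.20 |
| 2% | 40% | 0.192/0.98 = 19.59% | −0.41 |
| 5% | 10% | 0.195/0.95 = 20.53% | +0.53 |
| 5% | 20% | 0.190/0.95 = 20.00% | 0 |
| 5% | 30% | 0.185/0.95 = 19.47% | −0.53 |
| 5% | 40% | 0.180/0.95 = 18.95% | −1.05 |
| 5% | 62% | 0.169/0.95 = 17.79% | −2.21 |
| 8% | 10% | 0.192/0.92 = 20.87% | +0.87 |
| 8% | 40% | 0.168/0.92 = 18.26% | −1.74 |
| 8% | 62% | 0.1504/0.92 = 16.35% | −3.65 |

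If these women are dropped from both arms, or kept in both, the shift is 0.

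**False claims of non-inferiority.** Take 1571 per arm, a single look, a normal approximation and a true overall difference equal to the margin (24% against 20%), with f = 5% and r = 40% in both arms.
- One-sided drop: the half-dose rate is (0.24 − 0.02)/0.95 = 23.16%, a difference of 3.16 points. The chance of declaring non-inferiority is about 8.2%.
- Drop in both arms: the full-dose rate is 0.18/0.95 = 18.95%, a difference of 4.21 points. The chance is about 1.8%.
- All women kept: a difference of 4.00 points and a chance of 2.5%.

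**The case against.** The strongest reply is that the text sets one rule. A full-dose woman given the half-dose pack as rescue is also dropped, and a half-dose woman with an incomplete rescue is also kept. A reader might infer that the protocol selects the arms by different rules; it does not, and the asymmetry arises only from the kind of deviation likely to occur. A reader might also object that incomplete rescue is kept in full-dose women although it resembles the reduced regimen. That sentence covers both arms, requires the first course to be as randomised, and avoids a further post-randomisation exclusion, so it is defensible.

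Second, per-protocol deviations are always relative to the assigned regimen. A full-dose woman with a full rescue course has adhered, whereas a half-dose woman with one has crossed over. That is true, but it does not restore comparability once a masked event removes women from one arm only.

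Third, the route is inferred. Rescue is planned from same-arm packs, the statement that nothing is prohibited concerns other care, and the tracking of outside deliveries is there to limit loss to follow-up. Nothing says that packs are unavailable elsewhere or that off-pack rescue is given. This stands as a limit on how often the problem would arise.

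Fourth, off-pack rescue might be excluded in either arm as a failure to fulfil the protocol on interventions, or as overdose. That reading is possible, but the listed criteria do not say so, and the only one that names rescue as a ground for exclusion is relative to arm.

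**Conclusion.** The point holds as a defect in how the per-protocol criterion operates for off-pack full rescue courses. Its size cannot be fixed from the documents. With f between 1% and 5% and r between 10% and 62%, the shift runs from +0.53 to −2.21 points against a 4-point margin. At f = 8% it is −1.74 points for r = 40%, and the extremes of r widen the range to +0.87 and −3.65. The lower extreme assumes that rescued women fare like babies all born before 32 weeks.

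A reader might infer that the per-protocol result is biased towards non-inferiority. That follows only if the women removed are at above-average risk, which is plausible but not documented; at average risk the shift is nil, and below it the sign reverses. Nor is the trial's conclusion as a whole compromised: the intention-to-treat analysis is unaffected, the interim analyses are based on it, and no stated figure changes.

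**What to change.** In the per-protocol definition, replace the arm-relative treatment of off-pack rescue with one rule that does not depend on arm: exclude every woman, in either arm, who received betamethasone outside the allocated trial packs after randomisation. The existing criterion can remain for trial-pack errors, and the sentence on incomplete rescue courses need not change.

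Add a sensitivity analysis that defines the per-protocol set by eligibility and first course only and keeps all rescue courses. It should not be the main per-protocol analysis, because it retains half-dose women exposed to the full regimen and so brings back the dilution that the set is meant to remove.

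The cost is a change of wording, a slightly smaller per-protocol set, and recording off-trial betamethasone courses in both arms, including those given outside the investigation centres. The change concerns the analysis set only and has no bearing on how rescue is given.

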#### Interim analysis

To address the ethical concerns of (i) studying a high-risk population (pregnant women and preterm neonates), (ii) the potential increased rates of babies with severe RDS due to the reduction of the betamethasone dose, (iii) the anticipated length of time of inclusion (30 months), (iv) the number of infants planned for a fixed analysis (*n* = 3142) and (v) the primary endpoint measured in the first 48 h of life, a sequential data analysis method will be used, allowing to provide stopping rules. Analyses will be done after every 300 neonates who reach the primary outcome on the basis of intention to treat. The trial may be stopped for the following reasons:i.Inferiority of the experimental group on the primary outcome,ii.Non-inferiority of the experimental group on the primary outcome,

Finally, a maximum of 11 analyses is planned.

For the primary outcome, a non-inferiority sequential design with alpha and beta spending functions will be used to control the first type and second type error, respectively. For the estimation of the boundary curves, we chose a monotone function proposed by *Kim and DeMets* and generalized by *Jennison and Turnbull* [55, 56]. Critical values of the boundary curves are defined for each interim analysis. At each interim analysis, the maximum likelihood estimator of the difference of treatment failure rates between full-dose and half-dose will be compared to these critical values and the necessity to stop the trial will be checked.

In addition to that sequential primary analysis, the rate and percentage of the four safety outcomes (marked above with an *: neonatal death, IVH grade 3 and 4, NEC grade ≥ 2, and retinopathy of prematurity treated by anti-VEGF or laser) will be estimated in order to detect a potential increasing in the experimental group. Those estimation will be made on the overall population, and by gestational age at birth (born before 28 weeks, between 28 and 32 weeks, and after 32 weeks), as expected prevalence are different from one subgroup to the other.

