**Methods:**

A randomised, double blind, placebo-controlled, non-inferiority trial will be performed in 37 French level 3 maternity units. Women with a singleton pregnancy at risk of preterm delivery before 32 weeks of gestation having already received a first 11.4 mg injection of betamethasone will be randomised to receive either a second injection of 11.4 mg betamethasone (full dose arm) or placebo (half dose arm) administered intramuscularly 24 h after the first injection. The primary binary outcome will be the occurrence of severe respiratory distress syndrome (RDS), defined as the need for exogenous intra-tracheal surfactant in the first 48 h of life. Considering that 20% of the pregnant women receiving the full dose regimen would have a neonate with severe RDS, 1571 patients in each treatment group are required to show that the half dose regimen is not inferior to the full dose, that is the difference in severe RDS rate do not exceed 4% (corresponding to a Relative Risk of 20%), with a 1-sided 2.5% type-1 error and a 80% power. Interim analyses will be done after every 300 neonates who reach the primary outcome on the basis of intention-to-treat, using a group-sequential non-inferiority design.

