### Safety monitoring

The trial safety will be evaluated by an independent Data Safety Monitoring Board (DSMB) at each interim analysis or when additional analyses will be requested by the sponsor or the steering committee. The DSMB will include experts in or representatives of the fields of obstetrics, neonatology, and clinical trials methodology. At the first time they met, the DSMB will validate that the methodology is compatible with the safety of the participants. Prior to each DSMB meeting, they will be provided a complete list of all adverse events, and a statistical report including description of the population and results of the interim analysis as described above. At each meeting, the DSMB may give the advice to temporarily or definitely stop the trial if in their opinion there is an unexpected or unacceptable risk for the women or the newborn, or if the interim analysis suggests the non-inferiority or futility.

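### Early stopping for non-inferiority rests on intention-to-treat alone, although the primary analysis names both intention-to-treat and per protocol, and nothing says what follows if they disagree

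*Protocol article*

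**What the plan says.** Under Analysis population the article states: "The primary non-inferiority statistical analysis will be performed according to both the intention-to-treat and per protocol principle, as it is recommended for non-inferiority trials". ITT keeps women in their randomised arm "regardless of what treatment, if any, they received". PP removes, among others, women who received no intervention after randomisation and women given the opposite arm's product as first or rescue course.

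Under Interim analysis the population is ITT only: "Analyses will be done after every 300 neonates who reach the primary outcome on the basis of intention to treat". The abstract agrees: the looks are made "on the basis of intention-to-treat, using a group-sequential non-inferiority design". Reason (ii) for stopping is "Non-inferiority of the experimental group on the primary outcome". The decision uses one statistic: "the maximum likelihood estimator of the difference of treatment failure rates between full-dose and half-dose will be compared to these critical values". Under Safety monitoring the DSMB may advise stopping for an unacceptable risk, "or if the interim analysis suggests the non-inferiority or futility".

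The Final analyses section compares the final boundary with its critical value without naming a population. No section attaches a PP condition to the non-inferiority stop or deals with discordant results.

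**The concern.** The same hypothesis is tested on two populations in the primary analysis but on one at the looks where the trial may end. For an inferiority stop, ITT is a reasonable basis. For a non-inferiority stop the direction of bias matters.

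The arms differ only in the second injection. A full-dose woman who misses it has in effect received the half-dose regimen, and a woman given the other arm's product moves her arm towards the other. Both stay in ITT and leave PP, and both pull the ITT difference towards zero, which favours the claim.

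A stop ends recruitment. If PP on the same neonates then fails to support the claim, the trial is below its planned size, holds two primary results that disagree, and has no rule for reading them. The error at stake is accepting a less effective regimen.

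**Working it through.** **Inputs from the article (Sample size, Interim analysis).** Failure rate 20%, margin 4 points, one-sided alpha 0.025, power 0.80, 1571 per arm (3142 in all), looks every 300 neonates, at most 11 analyses.

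**The plan's own figures.** n per arm = 2 × 0.20 × 0.80 × (1.960 + 0.842)² / 0.04² = 1569.8, against 1571 stated. With 1571 per arm the standard error is √(2 × 0.16 / 1571) = 0.01427 and power is 0.800. 3142 / 300 = 10.5, which fits 11 analyses. These figures stand; the point concerns the stopping rule.

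**Assumptions.** The article gives neither a deviation rate nor the exact spending function. Let f be the proportional shrinkage of the ITT difference, with a true difference of exactly 4 points in women treated as assigned. The ITT difference is then 4(1 − f) points. If a share of the full-dose arm misses the second injection, f equals that share. If a share x of each arm receives the opposite product, f = 2x. Alpha is spent as 0.025 × t^ρ with ρ = 1, 2, 3, at 300, 600, …, 3000 and 3142 neonates, with no futility stop.

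**False ITT claim.** The single-look formula is P(Z > 1.96 − 0.04f / 0.01427). For f = 10%: 1.96 − 0.280 = 1.680, giving 4.7%. The 11-look figures are simulated.

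| f | ITT difference | Single look | 11 looks, ρ = 1 to 3 |
|---|---|---|---|
| 0 | 4.0 points | 2.5% | 2.5% |
| 5% | 3.8 points | 3.4% | 3.2–3.4% |
| 10% | 3.6 points | 4.7% | 4.1–4.6% |
| 20% | 3.2 points | 8.1% | about 7–8% |

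**Would PP catch these stops?** Suppose 5% of each arm receives the opposite product (f = 10%) and those women leave PP. With the true difference at the margin, an early ITT stop occurs in 3.9–4.0% of trials. In about 59–65% of those stops PP misses the same boundary at the same look. At 2.5% per arm the share is 42–45%.

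**How often does the early stop decide the trial?** With a true difference of 0, about 70–75% of trials stop early for non-inferiority on ITT. Under these assumptions the early stop is the main route to the claim.

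**Price of adding PP to the early stop.** With a true difference of 0 and 5% excluded from PP, the chance of an early stop falls from about 70–75% to 65–70%. PP misses at the same look in about a quarter of ITT stops, but most of those trials pass both at a later look. Adding a condition to a rule for claiming non-inferiority cannot raise its type-1 error.

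**Price of requiring both at the final analysis (fixed design, true difference 0).** The mean ITT z-value is 0.04 / 0.01427 = 2.803. With a share g excluded, the PP mean is 2.803 × √(1 − g) and the correlation is √(1 − g). The probability that both exceed 1.96 is about 76% for g = 5% and 74% for g = 10%, against 80% planned.

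**The case against.** A reader might infer that the article requires both populations to succeed, so that non-inferiority is by its own rule not shown when ITT passes and PP does not. The text does not support that: it says both analyses are performed and cites a recommendation, no more. There is therefore no flat contradiction. There is a stated interim rule narrower than the stated primary analysis, and silence on discordance. The Ethics section mentions an approved statistical plan, which may handle discordance. That softens the silence, but not the ITT-only basis that the article itself states for the looks.

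A reader might also infer that crossing forces a stop and that no later data can help. Stopping is discretionary, the DSMB can receive additional analyses if the sponsor or steering committee asks for them, PP is still to be reported, and the final analysis includes neonates who were not in the interim look. At 3142 women in 30 months, about 105 a month, some women would be randomised but undelivered at a stop. What stands is that recruitment ends and no rule covers a disagreement.

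Dilution is a risk, not a finding. A half-dose woman who misses the saline injection has still had the half dose, so non-receipt dilutes only in the full-dose arm, and ineligibility has no fixed direction. Randomisation just before the second injection, with identical packs, argues for few deviations. PP exclusions arise after randomisation and may carry selection bias, so PP belongs beside ITT, not in its place. All of this stands and limits the size of the point without removing it.

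**Conclusion.** The point holds in this form: a stop that ends recruitment can rest on one of the two populations named for the primary analysis, the one in which the relevant deviations would hide a difference, and the article does not say what follows if the other disagrees.

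For f of 5–10% the false ITT claim is about 3.2–4.6% instead of 2.5%. This rests on an assumed deviation rate, a true difference at the margin, and power-family spending with exponent 1 to 3; with few deviations the excess is small. The change is worth making because it is cheap and has to be in place before the first look.

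**What to change.** In Interim analysis, keep ITT as the basis for stop (i). For stop (ii), add that when the ITT estimate crosses, the PP estimate at the same look must also support non-inferiority against the same critical value; otherwise the trial continues to the next look. Align the abstract and Safety monitoring with this. In Final analyses, state which population governs the claim and how discordant results are handled.

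The cost is a sentence or two, one extra table per DSMB report from data already collected, and the modestly lower chance of early stopping shown above. Maximum size and boundaries do not change. If both populations are also required at the final analysis, restate the power (about 76% or 74% for 5% or 10% excluded, in a fixed design), since the sample size makes no allowance for it.
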